### Strategies to improve adherence to interventions

Medical notes (MN) of infants included in the study will be visibly marked to promote adherence to the study protocol. A flowchart explaining inclusion, exclusion and discontinuation criteria will be available in the patient's MN. A meeting will be scheduled to introduce the staff to the study protocol including:

Brief presentation of the study protocol such as justification for undertaking the trial and possible impact of the study outcome on everyday practice.Instructions about the way the intervention should be applied.

Reminder sessions will take place on a two-monthly basis at the departments where the study will be conducted. Staff will be asked about any problems they are experiencing with implementing the study.

### Relevant concomitant care permitted or prohibited during the trial

Participation in clinical trials involving interventions which may bias primary and secondary outcomes results will be prohibited.

### Outcomes

#### Primary outcomes

##### Necrotizing enterocolitis and death related to NEC

The primary outcomes will include Stage II or III of NEC as defined by Kliegman and Walsh (25) and death related to NEC.

Stage II NEC will be defined as distended abdomen and radiological symptoms (intramural and/or portal gas). Stage III NEC will be defined as distended abdomen, radiological symptoms (intramural and/or portal gas) and respiratory and cardiovascular failure requiring mechanical ventilation and inotropic support (25). In surgery verified cases no radiological verification will be required.

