## Methods and analysis

### Objectives

The aim of this study is to assess whether initiation and advancement of enteral feeding is safe, improves short term outcomes and does not increase the risk of NEC in neonates with duct dependant lesions.

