### Sample size

Studies have reported an incidence of NEC between 7–20% in babies with duct dependent congenital heart diseases, hence we chose the incidence of 18% in the control arm and 7.6% the intervention group (7, 14, 33–35). Therefore, 192 neonates should be included in each group. In total (assuming 20% lost for follow up), 384 neonates with a duct dependent heart disease should be included in the study. These calculations were performed assuming superiority *H0: P1* = *P2* vs. *H1: P1*≥*P2* with a power of 80%, a significance level of 5%. References: https://select-statistics.co.uk/calculators/sample-size-calculator-two-proprtions/ (36).

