### Blinding (masking)

Assessments regarding the clinical course will be conducted by an assessor blind to treatment allocation. Due to the nature of the intervention staff cannot be blinded to allocation but are strongly inculcated not to disclose the allocation status of the participant at the follow up assessments. A member of the research team blinded to treatment allocation will feed data into REDCap.

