### Statistical methods

#### Statistical methods for primary and secondary outcomes

As the trial is designed as a superiority study, both primary and secondary outcomes will be analyzed based on the per-protocol (PP) approach.

For primary outcomes and dichotomous secondary outcomes, between-group differences, and the two-sided 95% confidence interval (CI) for the estimated difference approach will be used (47–49).

For continuous outcomes, means/medians and 95% CIs will be calculated. Differences in changes from baseline between treatment groups will be compared using a two-sample t test or Mann-Whitney *U*-test (50).

Additionally, a predictive model to clarify the risk of NEC complications in both study groups will be implemented. Statistical and machine learning techniques such as decision trees, random forests, and support vector machine (SVM) will be used (51–55).

All statistical calculation will be carried out using R package (The R Foundation Vienna, Austria) and Statsoft (Hamburg, Germany).

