### Adverse event reporting and harms

We will define an adverse event (AE) as any untoward medical occurrence in a subject without regard to the possibility of a causal relationship. AE will be collected after the subject has provided consent and enrolled in the study. All AE occurring after entry into the study and until hospital discharge will be recorded. An AE that meets the criteria for a serious adverse event (SAE) between study enrolment and hospital discharge will be reported to the local Ethical Committee. A SAE for this study is any untoward medical occurrence that is believed by the investigators to be causally related to study-intervention and results in any of the following: Life-threatening condition (that is, immediate risk of death); severe or permanent disability, prolonged hospitalization. SAE occurring after a subject is discontinued from the study will NOT be reported unless the investigators feels that the event may have been caused by the study drug or a protocol procedure.

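### All-cause death is not a listed outcome, so a trial meant to show that the regimen is safe plans no between-arm comparison of deaths

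*Protocol article*

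**What the plan says.** **Aim.** The Objectives section sets out to "assess whether initiation and advancement of enteral feeding is safe". The Discussion anticipates a practice recommendation if the regimen does well.

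**Primary outcomes.** The primary outcomes are Stage II or III NEC "and death related to NEC". The Sample size section rests on NEC incidence alone: "we chose the incidence of 18% in the control arm and 7.6% the intervention group".

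**Secondary outcomes.** The list covers interrupted feedings, growth, vasoactive support, protein and energy intake, late-onset sepsis, days to full feeding, days ventilated, breastfeeding, cardiac parameters and age at transfer. Neither death nor survival is among them, and Table 1 has no row for vital status.

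**Harms.** Under Adverse event reporting and harms, every adverse event up to hospital discharge is recorded, whatever its cause. An SAE must be believed to be causally related to the intervention and must lead to one of these: "Life-threatening condition (that is, immediate risk of death); severe or permanent disability, prolonged hospitalization". Death is not on that list.

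**Analysis.** The Statistical methods section compares proportions as a between-group difference with a two-sided 95% CI, per protocol. ITT is a sensitivity analysis, and missing data are to be imputed. No rule covers an infant who dies without NEC.

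**The concern.** The Introduction describes a population prone to respiratory and cardiac failure, so deaths without NEC are foreseeable. An infant who dies first can no longer develop NEC. The primary comparison cannot register such a death as a harm, and no other planned comparison does so. If the study arm had more deaths of this kind, the listed outcomes would not show it, and the NEC proportion could even move slightly in that arm's favour. A conclusion that the regimen is safe would then rest on outcomes that leave out the most serious harm.

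**Working it through.** **1. The plan's own figure.** Inputs from the Sample size section: p1 = 0.18, p2 = 0.076, 5% significance (taken as two-sided, as in the analysis), 80% power, 20% loss.

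n = [1.96·√(2p̄(1−p̄)) + 0.8416·√(p1(1−p1) + p2(1−p2))]² / (p1−p2)², with p̄ = 0.128.

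n = (0.926 + 0.393)² / 0.104² = 161 per arm; with unpooled variance, 159. Multiplying by 1.2 gives 194 and 191, which bracket the stated 192. With 192 evaluable per arm, which the Recruitment section sets as the minimum, power for NEC is about 87%.

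**2. Effect of non-NEC deaths on the NEC comparison.** The documents give no non-NEC death rate, so d, the proportion dying of other causes before any NEC, is assumed. Let q be the NEC risk among the remaining infants, set at 18% in both arms so that there is no true NEC effect. With these infants kept in the denominator:

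- observed NEC = q(1−d)
- NEC or death = q(1−d) + d

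| Assumed d, control v study | Observed NEC | Difference, points | NEC or death | Difference, points | Non-NEC deaths per 192 |
|---|---|---|---|---|---|
| 5% v 5% | 17.1% v 17.1% | 0.0 | 22.1% v 22.1% | 0.0 | 9.6 v 9.6 |
| 5% v 10% | 17.1% v 16.2% | −0.9 | 22.1% v 26.2% | +4.1 | 9.6 v 19.2 |
| 5% v 15% | 17.1% v 15.3% | −1.8 | 22.1% v 30.3% | +8.2 | 9.6 v 28.8 |
| 5% v 20% | 17.1% v 14.4% | −2.7 | 22.1% v 34.4% | +12.3 | 9.6 v 38.4 |

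Differences are study minus control. For 5% v 15%: 0.18 × 0.95 = 0.171 and 0.18 × 0.85 = 0.153; adding 0.05 and 0.15 gives 0.221 and 0.303.

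**3. Other ways of handling these infants.** If they are excluded, NEC is 17.1/95 = 18% v 15.3/85 = 18%. If their NEC status is imputed from the other infants in the same arm, the expected value is again 18% v 18%. Neither route favours the arm with more deaths, but neither shows the excess.

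**4. What a direct comparison of deaths would show.** Wald 95% CI with 192 per arm:

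- 10% v 5%: 5 ± 1.96·√[(0.10·0.90 + 0.05·0.95)/192] = 5 points (−0.2 to 10.2)
- 15% v 5%: 10 points (4.1 to 15.9)

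An excess of the second size would be clear in an all-cause death outcome, yet it enters no listed outcome.

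**5. Power of NEC or any death as a composite.** Design NEC rates, equal d in both arms, 192 evaluable per arm:

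power = Φ{[Δ√192 − 1.96·√(2p̄(1−p̄))] / √(p1(1−p1) + p2(1−p2))}

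| d | Composite rates | Power |
|---|---|---|
| 2% | 19.6% v 9.5% | 81% |
| 5% | 22.1% v 12.2% | 73% |
| 10% | 26.2% v 16.8% | 61% |
| 15% | 30.3% v 21.5% | 51% |

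**The case against.** **Safety data are collected.** In-hospital deaths fall under the broad adverse event definition. An independent DMC monitors safety and may ask for further analyses, and all randomised infants are to be followed to 12 months. This stands: a reader might infer that an excess of deaths could never be seen, and the documents do not support that. What is missing is a planned comparison. Adverse event recording stops at discharge, and the interim analyses specified are on the primary endpoint.

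**The handling of competing deaths is not stated and may be in an unseen SAP.** This also stands. That a death counts as NEC-free is one reading of the analysis, not a rule in the protocol. The choice of outcomes, however, belongs in the protocol, and its list is complete without all-cause death.

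**The distortion of NEC is small.** Also correct: 0.9 to 1.8 points when non-NEC mortality doubles or triples, against a design difference of 18 − 7.6 = 10.4 points. Nothing in the documents suggests that a feeding protocol would have such an effect. The main defect is the absent death comparison rather than bias in NEC.

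**Attribution of deaths.** Because "Due to the nature of the intervention staff cannot be blinded to allocation", a reader might infer that relabelling a few deaths as unrelated to NEC would shift the primary result. The documents do not support that. The same section provides a blinded assessor of the clinical course. A death related to NEC will normally be in an infant already counted with Stage II or III disease, so relabelling leaves the NEC count unchanged; it matters only if NEC-related death is analysed separately or NEC was never staged. Expected NEC deaths of 192 × 0.18 × 0.24 = 8.3 and 192 × 0.076 × 0.24 = 3.5 are upper bounds, because the Introduction gives 24% as the top of its mortality range.

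**Conclusion.** The point holds in this form: NEC-related death is the only mortality outcome, death is not a named SAE consequence, and no between-arm comparison of deaths is planned in a trial with a stated safety aim. A death without NEC never counts against an arm, whichever way the infant is handled.

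The size depends on non-NEC mortality, which the documents do not give. At an assumed 5% v 15% with equal NEC risk, the NEC comparison would favour the study arm by 1.8 points while NEC or death would be 8.2 points worse. With similar mortality in both arms the NEC comparison is not distorted. This limits what the trial can conclude about safety; it does not invalidate the primary outcome or the sample size.

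**What to change.** 1. Add all-cause death as a secondary safety outcome, reported by arm with a 95% CI, over the window used for the primary outcome and to 12 months.
2. Name death among the SAE consequences.
3. Pre-specify a sensitivity analysis of NEC Stage II/III or death from any cause in all randomised infants, so that no death counts as a success.
4. Leave the primary outcome and the sample size as they are.

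**Cost.** Vital status must be recorded at the planned follow-up visits. Table 1 does not list it, and the protocol allows for up to 20% annual loss to follow-up, so it cannot be assumed to be already available. The composite is less specific to NEC and less powerful: about 73% at 5% and 61% at 10% non-NEC mortality with 192 evaluable per arm. It should therefore be supportive only, and a result that does not reach significance should not be read as evidence of safety.

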**Methods:**

This randomized control trial will recruit term infants diagnosed with a duct dependant lesion within the first 72 h of life. After obtaining written parental consent patients will be randomized to either the physician led enteral feeding or protocol-based feeding group. The intervention will continue up to 28 days of life or day of cardiosurgical treatment, whichever comes first. The primary outcomes include NEC and death related to NEC. Secondary outcomes include among others, number of interrupted feedings, growth velocity, daily protein and caloric intake, days to reach full enteral feeding and on mechanical ventilation.

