#### Interim analyses

Our study is a multicentre study, located in 4 different unit. Three interim analyses (IA) will be performed on the primary end point every 100 recruited patients. IA will be conducted by an independent statistician, blinded for the treatment allocation. This will allow us to track trial data collected on case report forms and generate performance metrics. Additionally, it will make data and study information available in a timely manner and re-estimate the sample size if needed. Results of interim analyses will be reported to the DMC, which will decide whether the trial should be continued or stopped for futility based on the pre-specified criteria. The Peto approach will be used: the trial will be ended using symmetric stopping boundaries at *P* < 0.001 (56).

Additionally, sensitivity analysis for the primary outcomes will be carried out with an intention-to-treat (ITT) approach. Protocol deviations will be reviewed by a blinded adjudication DMC who will decide by consensus whether a patient should be included in the ITT or per protocol population. We do not plan any subgroup analyses. In case of missing data, standard data imputation algorithms will be used (e.g., multiple imputation) (55).

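### NEC and NEC-related death are both called primary, but the sample size, the 5% level and the 80% power fit the trial only if NEC alone decides it.

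*Protocol article*

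**What the plan says.** All references are to the protocol article.

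- **Abstract, Methods:** "The primary outcomes include NEC and death related to NEC".
- **Primary outcomes:** "The primary outcomes will include Stage II or III of NEC", and the same sentence adds NEC-related death. Both items stand under one sub-heading, and the sentence is in the plural.
- **Statistical methods for primary and secondary outcomes:** "For primary outcomes and dichotomous secondary outcomes, between-group differences, and the two-sided 95% confidence interval (CI) for the estimated difference approach will be used". No order, split of the 5% or decision rule is given.
- **Sample size:** "hence we chose the incidence of 18% in the control arm and 7.6% the intervention group", with 80% power, a 5% level, 20% loss and 192 infants per arm. No death rate and no effect on death enters.
- **Interim analyses:** "Three interim analyses (IA) will be performed on the primary end point every 100 recruited patients", in the singular. The Allocation section also uses the singular for the primary endpoint. Later in Interim analyses, the sensitivity analysis is again for plural primary outcomes.
- **Background and rationale:** the only mortality figure is a rate of up to 24%, given next to the incidence of NEC in congenital heart disease.

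**The concern.** The article does not agree with itself on whether there is one primary outcome or two, and the design figures match only one of the readings. There are three ways to read it: success on either outcome is enough, success on both is required, or the two form one composite. They have different error rates and different power, and the article does not choose among them.

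This matters when the two results differ. A clear difference in NEC with a wide interval around a handful of deaths is the likely pattern, and the reverse can also occur. Nothing in the article says which result then decides the trial, or to which outcome the interim boundary of P < 0.001 applies.

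**Working it through.** **Inputs.** NEC 18% v 7.6%, two-sided 5%, 80% power, 20% loss and 192 per arm are from Sample size. Case fatality of 24% is an assumption: it is the upper limit in Background and rationale, read as the share of NEC cases that die. The relative effect on death is assumed equal to that on NEC. Case fatalities of 10% and 5% are further assumptions, used to show the range.

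**1. The plan's own figure.** Here d = 0.18 − 0.076 = 0.104 and the mean rate is 0.128.

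- Pooled formula: n = [1.960·√(2·0.128·0.872) + 0.842·√(0.18·0.82 + 0.076·0.924)]² / 0.104² = 160.8, so 161 per arm.
- Unpooled formula: 158.07, so 159 per arm.
- Multiplied by 1.20: 194 and 191.

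The stated 192 lies between these (160 × 1.20 = 192). It is therefore reproduced from NEC alone, with a two-sided test.

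**2. Power for NEC.** Power = Φ[(d − 1.960·SE₀)/SE₁], where SE₀ is the pooled and SE₁ the unpooled standard error.

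- 192 evaluable per arm: Φ[(0.104 − 1.960·0.03410)/0.03368] = 86.5%.
- 160 per arm: 79.8%.
- 154 per arm (192 less 20%): 78.3%.

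**3. Power for NEC-related death.** Rates at 24% fatality are 0.24 × 18% = 4.32% and 0.24 × 7.6% = 1.82%. With 192 per arm, that is about 8.3 v 3.5 expected deaths.

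- 192 per arm: Φ[(0.02496 − 1.960·0.01761)/0.01757] = Φ(−0.544) = 29.3%.
- 160 per arm: 25.2%.
- 154 per arm: 24.4%.
- 10% fatality (1.8% v 0.76%), 192 per arm: about 15%.
- For 80% power at 24% fatality: about 750 evaluable per arm.

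For a fair comparison, the two powers must be read at the same n: about 87% and 29% at 192, or about 80% and 25% at 160.

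**4. Either outcome suffices.** Two independent 5% tests would give 1 − 0.95² = 9.75%. The two outcomes are correlated, because the deaths are a subset of the NEC cases. Simulating equal arms with deaths nested in NEC (400,000 trials per scenario, z-type test, NEC 12.8% or 18%, 24% fatal, 192 or 154 per arm) gives about 8.7 to 9.3%. Two things lower this:

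- At 5% fatality and 192 per arm, it is 5.6 to 8.3% for NEC between 7.6% and 18%.
- With Fisher's exact test at 24% fatality and 192 per arm, it is 4.3 to 5.9%.

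**5. Both must succeed.** Under no effect on either outcome, both tests reject in about 0.7 to 0.8% of simulated trials at 24% fatality, so the 5% is not exceeded. Joint power at 18% v 7.6% and 24% fatality is about 28% at 192 per arm and 21% at 154.

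**6. Composite.** A death related to Stage II or III NEC is already a NEC case. The composite therefore counts essentially the same infants as NEC, with one test and the power in step 2.

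The interim looks at P < 0.001 are left out of all these figures.

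**The case against.** The strongest objection is that a single-endpoint reading has support in the text. Both items share one sub-heading while the secondary outcomes have their own, and the Allocation and Interim analyses sections use the singular. On that reading the endpoint equals NEC, the sample size fits it, and nothing is inflated or underpowered. This stands as a possible reading. It does not settle the matter, because the plural appears in the abstract, Primary outcomes and Statistical methods, and again in Interim analyses, and the article nowhere calls the two a composite.

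A reader might infer more than the article supports:

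- **That the trial's type I error is 9%.** This needs an either-outcome rule, which is not stated, and a z-type interval. The article does not name the interval method.
- **That 80% power is claimed for death.** It is not; the Sample size section ties the 80% to the incidence of NEC.
- **That 29% is the expected power for death.** It is a best case, because 24% is an upper limit.
- **That the deciding outcome will be picked after the data are seen.** The analysis plan is not shown and may hold an order or a split of the 5%.

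The last point does not remove the concern. Which outcome is primary, and whether the sample size matches it, are stated in this article, and the statements do not agree. On the article's figures and the assumptions above, no later adjustment could give a trial of this size 80% power for NEC-related death.

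**Conclusion.** The concern holds as an inconsistency to resolve. The stated 5% and 80% describe this trial only if NEC alone decides it, which is also what a composite amounts to. Under an either-outcome rule the error is up to about 9%. Under a both-outcomes rule the error is kept, but power is at most about 28% at 192 evaluable per arm, or 21% at 154. Power for NEC-related death alone is at most about 29% at 192 per arm and about 24 to 25% at 154 to 160.

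These upper values rest on 24% case fatality and an equal relative effect on death and NEC; lower fatality reduces the power. Power for NEC itself is not in doubt on the planned rates: about 87% at 192 evaluable per arm and about 80% at 160.

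**What to change.** Name one primary outcome: NEC Stage II or III, fatal or not. This is the outcome that the sample size already uses, and the interim analyses should be said to monitor it. List NEC-related death as a secondary outcome, reported with its confidence interval and no claim of 80% power. Use the singular throughout the abstract, Primary outcomes, Statistical methods and Interim analyses.

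An explicit composite, or a fixed order with NEC tested first, would also remove the ambiguity. The composite would add essentially no events, and the fixed order would leave death with the low power shown above.

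The cost is wording in the protocol and the analysis plan. The design and the sample size stay as they are. The downside is that NEC-related death loses its primary label.

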#### Secondary outcomes

##### Number of interrupted feedings

Number of interrupted/discontinued feedings per day.

### Growth

Impact on raw and z-score weight, length, and head circumference will be assessed Measurements will be collected at 3, 6 and 12 months of age and reported as z-scores (26).

### Vasoactive support (VA)

Because concomitant use of multiple VA's is common in this group of patients, the vasoactive inotropic support score (VIS) will be calculated to quantify the vasoactive support. The daily VIS will be collected for the complete study period, using the updated definition from Gaies (27). VIS has been previously used to assess enteral feeding safety in a population of critically ill pediatric patients (28). Along the daily scores, the highest VIS and mean VIS will also be calculated.

### Daily protein and caloric intake

Daily intakes of energy (Kcal/kg) and protein (g/kg) provided by enteral and parenteral feeding will be calculated.

